# Effects of transcutaneous electrical phrenic nerve stimulation and transcutaneous electrical diaphragmatic stimulation: A protocol for a randomized, single-blind, crossover trial

**DOI:** 10.1371/journal.pone.0347493

**Published:** 2026-04-27

## Abstract

**Background:**

Patients in the intensive care unit (ICU) are at high risk of developing respiratory muscle weakness, which may lead to prolonged mechanical ventilation and worsening clinical outcomes. Noninvasive neuromuscular electrical stimulation techniques, such as transcutaneous electrical phrenic nerve stimulation (TEPNS) and transcutaneous diaphragmatic electrical stimulation (TDES), offer potential therapeutic options for patients unable to generate voluntary active contractions. However, there is limited research directly comparing the effects of these modalities on diaphragmatic function. The primary objective of this study is to evaluate the effects of TEPNS and TDES on diaphragmatic function in healthy adults. Secondary objectives include assessing the safety, feasibility, and perceived discomfort associated with the application of each technique.

**Methods:**

This study will be a bicentric, randomized, single-blind, crossover trial that will be conducted at two hospitals in São Paulo, Brazil. Healthy adults aged 18–60, with a BMI between 18.5 and 24.9 kg/m^2^, no history of respiratory diseases, and no contraindications for the proposed electrical stimulation modalities will be included. Diaphragm thickness, thickening fraction, and mobility will be assessed using ultrasound during tidal breathing. Participants will be randomly assigned to begin the intervention with one of two experimental conditions: (1) TEPNS protocol or (2) TDES protocol. In addition, data on the safety and feasibility of each electrical stimulation modalities will also be collected.

**Trial registration:**

This protocol is registered at ClinicalTrials.gov under the number NCT06339632.

## Introduction

Critically ill patients are at high risk of developing both respiratory and limb muscle weakness [1]. Intensive care unit (ICU)-acquired muscle weakness is a well-established and common condition for limb muscles, strongly associated with poor clinical outcomes [2,3]. In contrast, the impact of respiratory muscle weakness has been less extensively studied; however, emerging evidence suggests it may contribute to prolonged mechanical ventilation (MV) support [4], an increased risk of ICU readmission [5], and higher mortality rates [6]. Diaphragm dysfunction affects more than 60% of patients undergoing MV support [7] and is associated with difficult and prolonged weaning from MV, as well as unfavorable clinical outcomes [4].

Over the past few years, several techniques have been proposed and developed to address respiratory muscle weakness, including invasive methods designed to induce diaphragm muscle contractions in patients with respiratory failure or muscle weakness [8,9]. These techniques, classified as transvenous approaches, involve the stimulation of the phrenic nerve—which controls the diaphragm movement—through electrodes surgically inserted into the internal jugular or subclavian [8–10]. This allows for direct activation of the diaphragm. However, invasive phrenic nerve stimulation methods present several drawbacks that limit their use in clinical practice. These include the risks of complications and adverse events such as hematoma, pneumothorax, thrombosis, and infection at the catheter insertion site [11].

Neuromuscular electrical stimulation (NMES) is a non-volitional and noninvasive therapeutic approach developed to prevent and treat muscle weakness. This technique involves the application of electrical stimuli through surface electrodes to induce effective muscle contractions [12,13]. Because NMES does not require active patient participation from the patient to elicit muscle contraction, it can be used even in clinical situations where the patient is under sedation and analgesia [12]. In this context, transcutaneous electrical phrenic nerve stimulation (TEPNS) and transcutaneous diaphragmatic electrical stimulation (TDES) have emerged as noninvasive modalities to induce contractions in diaphragm muscle fibers [14], offering a safer alternative to invasive techniques and procedures.

Noninvasive stimulation of diaphragm contraction has been investigated, however, the heterogeneity of protocols and NMES parameters used—combined with the anatomical complexity of locating the diaphragm’s motor point—limits the reproducibility and clinical applicability of this technique [15–17]. Therefore, the primary objective of this study is to compare the effects of TEPNS and TDES on diaphragm thickness, thickening fraction, and diaphragmatic mobility in healthy adults.

## Methods

### Study design

This study will be a bicentric, randomized, single-blind, crossover trial, approved by the local Ethics Committee of the Hospital Sírio-Libanês (approval number 6.631.794, approved on February 1, 2024). The study is currently in the participant recruitment phase, which began on April 1, 2024, and has not yet generated any results, with recruitment expected to be completed by July 2027. The study protocol was prospectively registered in the *ClinicalTrials.gov* database (NCT06339632) and structured in accordance with the *Standard Protocol Items: Recommendations for Interventional Trials 2025* —SPIRIT 2025 guidelines (S1 File). The overall schedule and time commitment for trial participants are depicted in **Fig 1** and the study design is illustrated in **Fig 2**.

**Fig 1 pone.0347493.g001:**
[figure not shown]
SPIRIT diagram.

**Fig 2 pone.0347493.g002:**
[figure not shown]
Flow diagram of the crossover trial. TEPNS: transcutaneous electrical phrenic nerve stimulation; TDES: transcutaneous diaphragmatic electrical stimulation.

Participants will be recruited from the city and metropolitan region of São Paulo through announcements on corporate and institutional communication printed and electronic media distributed across the hospital units and educational facilities of Hospital Sírio-Libanês and Hospital Israelita Albert Einstein. Recruitment and initial contact will be conducted remotely. Prospective participants will be instructed to complete an initial application form, accessible via a link to the Research Electronic Digital Capture (REDCap) system. This form will provide an overview of the study’s scope and objectives, followed by a request for registration information. Eligible individuals will be contacted by the research team to provide written informed consent. Upon signing the written informed consent form, participants will be scheduled for a screening visit.

Inclusion criteria will require participants to be between 18 and 60 years of age, have normal pulmonary function as assessed by spirometry, and a body mass index (BMI) between 18.5 and 24.9 kg/m^2^. Exclusion criteria include current or former smokers; individuals with known cardiorespiratory diseases such as restrictive pulmonary diseases, chronic obstructive pulmonary disease (COPD), asthma, cystic fibrosis, or related conditions; individuals with implanted electrical devices, including pacemakers or implantable cardioverter-defibrillators; and individuals with contraindications to transcutaneous electrical stimulation or diaphragmatic assessment. Contraindications may include altered sensitivity, wounds at the application site, anatomical deformities, or other medical conditions.

Eligible participants will undergo a screening process to confirm compliance with the inclusion criteria. This includes a demographic interview, pulmonary function test using a calibrated Koko^®^ spirometer (PFT System), assessment of maximum inspiratory pressure (MIP), forced vital capacity (FVC) and BMI measurement. Pulmonary function tests will be conducted in accordance with the guidelines of the American Thoracic Society and the European Respiratory Society [18]. Participants exhibiting abnormal pulmonary function indicative of obstructive or restrictive disease, or a BMI outside the established range, will be excluded from the study.

### Sample size

Since no previous studies have evaluated the effects of this specific intervention on the diaphragm thickness, an initial pilot phase including 12 participants will be conducted to obtain preliminary estimates of variability and treatment effect. These data will be used to inform a formal sample size calculation for the main crossover trial. The primary outcome for sample size determination will be diaphragm thickness. The sample size calculation will be based on the expected within-participant mean difference between intervention conditions and the corresponding standard deviation derived from the pilot data, assuming a paired t-test framework. The required sample size will be estimated considering a two-sided significance level of 5% (α = 0.05) and a statistical power of 80%. Additionally, a potential dropout rate of approximately 20% will be incorporated to ensure adequate statistical power for the final analysis.

### Randomization and allocation

To minimize the potential influence of age on the results, initial allocation in this crossover study will be randomized in a balanced manner according to participants’ age, using three predefined age groups: (i) 18–35 years, (ii) 36–46 years, and (iii) 47–60 years, according to screening database. Participants will be randomly assigned to begin the intervention with either the TEPNS or TDES protocol. Randomization will be performed using a sealed-envelope method with sequentially numbered, opaque envelopes prepared according to a block randomisation scheme (block size = 4). Envelopes will be opened immediately prior to the baseline ultrasonography assessment. This procedure ensures balanced allocation and an equal probability (1:1) of initiating the intervention with either the TPNS or the TDES protocol.

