### Intervention

The intervention will be conducted in two different times, depending on the randomization sequence, and may begin with either TEPNS or TDES. A 1-hour washout period will be conducted between the two interventions. During interventions, participants will be instructed to breathe normally at tidal volume, using the perception of the electrical current as a cue for the onset of inspiration. This ensures synchrony with the stimulation cycle (“on” and “off” times), without altering the participant’s natural respiratory rhythm or pattern. For both the TEPNS and TDES, electrical stimulation will be applied continuously for 10 minutes in a single session.

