### Statistical analysis

The Research Electronic Data Capture (REDCap) platform will be used for data entry and storage. Continuous variables will be reported as mean ± standard deviation (SD) for normally distributed data, or as median and interquartile range (IQR, 25th–75th percentile) for non-normally distributed data. Categorical variables will be presented as absolute numbers and percentages. Normality will be assessed using the Shapiro–Wilk test. For within-participant comparisons between TEPNS and TDES conditions, paired t-tests will be used for normally distributed data, and the Wilcoxon signed-rank test will be applied for non-parametric data. The primary analysis will be performed using a linear mixed-effects model appropriate for a two-period crossover design, including treatment, period, and sequence as fixed effects, and participant as a random effect, thereby accounting for within-subject correlation. Percentage changes in diaphragm thickness, thickening fraction, and mobility will also be calculated.

The frequency of adverse events will be systematically recorded and descriptively analyzed to characterize the safety profile of both interventions. Additionally, associations between diaphragm thickness, thickening fraction, diaphragmatic mobility, stimulation intensity, participant-reported discomfort, and the occurrence of adverse events will be explored using Pearson’s or Spearman’s correlation coefficients, as appropriate. Adjustment for multiple comparisons will be performed where applicable to control the risk of type I error. Missing data will be addressed using multiple imputation by chained equations under the missing-at-random assumption. Each imputed dataset will be analyzed separately, and the results will be pooled using Rubin’s rules to obtain valid statistical inferences.

All statistical analyses will be performed using the Statistical Package for the Social Sciences (SPSS) version 28.0.1 (SPSS Inc., Chicago, IL, USA). A two-sided p-value < 0.05 will be considered statistically significant. The statistician responsible for data analysis will be blinded to the allocation sequence and intervention timing.

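### The primary model omits age group × period although sequence is stratified by age, so if period effects differ by age the reported standard error is slightly too wide (minor)

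*Protocol article*

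**What the plan says.** Under Randomization and allocation, the starting intervention is "randomized in a balanced manner according to participants’ age, using three predefined age groups" (18–35, 36–46 and 47–60 years), in blocks of four with "an equal probability (1:1) of initiating the intervention" on either technique. The section opens with the aim: "To minimize the potential influence of age on the results, initial allocation in this crossover study will be randomized in a balanced manner".

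Under Statistical analysis, the primary analysis is a linear mixed model "including treatment, period, and sequence as fixed effects, and participant as a random effect". Age group is not among the terms, either alone or with period. The other analyses listed there (paired tests and exploratory correlations) do not use it either.

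Under Intervention, the two sessions fall close together: "A 1-hour washout period will be conducted between the two interventions". Under Sample size, "an initial pilot phase including 12 participants will be conducted", and the final number of participants will be set from that pilot. No section gives a final number, a standard deviation or an effect size, and none says whether period effects are expected to vary with age.

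**The concern.** A factor used to restrict randomisation normally appears in the analysis, so that the standard error reflects the balance the design has bought. Here the design names age as something to guard against, and the model, whose terms are listed one by one, leaves it out.

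In a crossover the question is narrower than in a parallel trial. Each participant serves as their own control, so an overall difference between younger and older people drops out of the comparison. Balancing sequence within age groups protects against one thing only: a change from the first to the second session that differs by age, for example through habituation to the current or tiring. If that happens, the stratification removes the variation from the estimate, but the model leaves it in the residual. What is at stake is a confidence interval somewhat wider than it need be and a test run somewhat below its nominal 5%.

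**Working it through.** The document states no standard error, SD or final N, so there is no planned figure to reproduce.

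**Inputs from the protocol article.** Three age groups, blocks of four, 1:1 sequences, two-sided 5% level, and the model terms quoted above.

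**Assumptions not in the document.** Equal age groups; a separate envelope series for each age group (implied, not stated); complete pairs; period effects shifted by −h, 0 and +h across the age groups, with h in units of the SD of the paired difference (τ); N of 24 to 36.

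**Step 1: which age term matters.** Mixed models were fitted to simulated crossovers with n = 36 and sequence balanced within each age group.

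| Simulated data | Model as written: SE | + age main effect | + age group × period |
|---|---|---|---|
| Age main effect only | 0.1807 | 0.1807 | 0.1814 |
| Age × period also present (deliberately strong) | 0.3121 | 0.3121 | 0.2495 |

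The treatment estimate is the same under all three models within each row (0.7367 in the first, 0.1181 in the second). The age main effect does nothing; only age group × period changes the standard error.

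**Step 2: closed form.** Take each participant's second-minus-first-period difference, with SD τ within an age group. With sequence balanced in each age group:

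- true SE = τ/√n
- variance between age groups of the period difference = (h² + 0 + h²)/3 × τ² = (2/3)h²τ²
- reported SE ÷ true SE ≈ √(1 + 2h²/3)

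This gives:

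- h = 0: ratio 1.00
- h = 0.4: √(1 + 0.107) = 1.05
- h = 0.6: √(1 + 0.240) = 1.11

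At n = 30 and τ = 1, the true SE is 1/√30 = 0.183, and the model as written would report about 0.192 and 0.203.

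**Step 3: simulation at n = 30.** There were 10 participants per age group in blocks of four, with 6,000 runs per setting. Power is for a treatment difference of 0.6τ.

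| h | Model as written: mean SE | True SE | Type I error | Power | With age group × period: SE | Type I error | Power |
|---|---|---|---|---|---|---|---|
| 0.4 | 0.191 | 0.185–0.187 | 4.2% | 86.7% | 0.182 | 5.1% | 88.7% |
| 0.6 | 0.203 | 0.185–0.187 | 3.2% | 82.7% | 0.182 | 5.1% | 88.2% |

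The true SE is a little above 0.183 because ten is not a multiple of four, so last blocks may be incomplete. Inflation is then 0.191/0.185 = 1.03 and 0.203/0.187 = 1.09, slightly below the closed form. Over n = 24 to 36 the range is about 3–5% at h = 0.4 and 8–12% at h = 0.6.

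**Step 4: does stratifying help at all?** At n = 24, with shifts of one within-participant SD (h = 1/√2 = 0.71), the true SE is 0.289 with stratification and 0.336 without. The model as written reports about 0.337 and 0.336. The precision is gained but not shown.

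**Step 5: cost of the term when h = 0.** The residual degrees of freedom fall from n − 2 to n − 4. From the noncentral t distribution with noncentrality 0.6√n, power goes from 80.2% to 79.8% at n = 24 and from 46.8% to 44.8% at n = 12. Simulation with blocks of four puts the loss at about 0.5 to 0.7 points at n = 30 and about 3 points at n = 12.

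**The case against.** The strongest reply is that the design already does the work. Participant is in the model, the age main effect cancels, and no section suggests that period effects vary with age. The sessions last ten minutes, and the Discussion expects the effects to be short-lived. The assumed shifts are also large: at ±0.4 and ±0.6 the youngest and oldest groups differ by 0.8 and 1.2 SD of the paired difference, more than the 0.6 SD treatment effect in the same simulation. Planned power is partly protected too, because the pilot SD of the within-participant difference would already contain any such variation. Finally, interaction terms are often left to an analysis plan, which is not shown.

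Most of this stands and limits the size of the point. It does not remove it. The article lists the terms of the primary model, so the omission is a stated choice and not a missing detail. If age is thought unable to act through the period effect, stratifying by it has little analytic purpose; if it can, the model should reflect it.

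A reader might infer three stronger things that the document does not support:

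- **That the stratification gains no precision.** Step 4 shows that it does when period effects differ by age; only the reported standard error fails to show it. When they do not differ, there was nothing to gain and the standard error is right.
- **That the primary test is invalid.** The error runs in the conservative direction only.
- **That the trial cannot examine the role of age.** Age group is held for randomisation and nothing rules out an exploratory look. The stated aim is to limit the influence of age, not to estimate it.

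**Conclusion.** The point holds as a minor, conditional matter of efficiency. The primary model does not contain the stratum in the one form that affects the standard error of a crossover comparison, age group × period. If period effects differ by age, the reported standard error is too wide by about 3–5% at shifts of ±0.4 SD of the paired difference and 8–12% at ±0.6 SD, with type I error of about 4% and 3% (n = 24 to 36). At n = 30 the power forgone is 88.7 − 86.7 = 2.0 points and 88.2 − 82.7 = 5.5 points.

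These sizes rest wholly on the assumed shifts, on equal age groups and on the assumed N; the document gives none of them. With no age difference in period effects, reported and true standard errors agree. In no case examined is there bias or type I error inflation.

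**What to change.** In Statistical analysis, add age group and age group × period to the primary mixed model of the main trial, so that the analysis matches the stratified randomisation. Adding the age main effect alone would change nothing in complete pairs. If the investigators prefer to leave age out, one sentence giving the reason (its main effect cancels, and period effects are not expected to vary with age) would settle the point.

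The cost is a line of text and 2 degrees of freedom: under 1 point of power at n = 24 to 36 if age plays no part, and about 2 to 3 points at n = 12. The change therefore suits the main trial and not the 12-person pilot. No new data are needed, because age group is already recorded. The article reports that recruitment is under way with no results yet, so the model can still be changed without knowledge of outcomes. A treatment × age group estimate with its confidence interval is optional.

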### Blinding

Blinding participants to the TEPNS or TDES intervention is not feasible, as most individuals can perceive the electrical stimulation, and visible muscle contractions are required to confirm proper electrode placement. However, ultrasound images will be analyzed by a researcher who is blinded to the intervention procedure and image acquisition. Additionally, all file names will be coded and will not indicate the group to which the participant was allocated.

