### Outcome measures

#### Diaphragmatic ultrasonography.

Diaphragmatic assessments will be performed using a LOGIQ E^®^ (R7) ultrasound system equipped with linear (GE12L-RS, 13 MHz) or a convex transducer (C1-5-D), in conjunction with water-based gel. Participants will be evaluated in supine position with a 30 degrees trunk inclination. Diaphragmatic mobility, thickness, and thickening fraction will be assessed. To measure tidal volume during the intervention, a facial mask will be connected to a ventilometer and a HEPA-filtered. The facial mask will be placed by the evaluator one minute before the assessment, and during two specific intervals: between the 4th and 5th and between the 9th and 10th minute of the intervention. Ultrasound evaluations will be conducted during spontaneous ventilation at tidal volume during both intervals, according to the randomization protocol.

Measurements of diaphragm mobility, thickness, and thickening fraction will be averaged from multiple respiratory cycles within the following three time points: (i) baseline (pre-intervention), (ii) 4–5 minutes into the intervention, and (iii) 9–10 minutes post-intervention. All ultrasound images will be exported to a secure storage device designated for research purposes only, with access restricted to authorized study personnel and researchers. While blinding is not feasible during image acquisition, a blind evaluator–who is not involved in the intervention or image collection–will perform the image analysis.

Diaphragmatic mobility will be assessed using a convex transducer (2–6 MHz) positioned in the right subcostal region along the mid-clavicular line, angled cephalically (**Fig 4A****-****4C**). Initially, B-mode ultrasound will be used to locate the diaphragmatic hemi-cupola. Once identified, M-mode will be employed to measure respiratory excursions, using the inferior vena cava and gallbladder anatomical landmarks. Mobility will be quantified as the vertical distance between the baseline position during expiration and the point of maximal diaphragmatic displacement during inspiration [22,23].

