Despite the strengths, some limitations should be acknowledged. The study will be conducted with a sample of health volunteers, which may limit the generalizability of the findings to critically ill patients. Healthy volunteers were defined as the initial study population to allow a controlled evaluation of feasibility, safety, and discomfort, prior to assessing the outcome of the intervention in critically ill patients. However, this approach may limit the external validity and generalizability of the findings. The nature and characteristics of the intervention was not designed to evaluate long term clinical outcomes. The findings of this study should be interpreted within the context of the specific sample, as they are limited to participants recruited from two hospitals in São Paulo, Brazil. Therefore, further studies with larger sample sizes and conducted across different geographic settings are warranted to confirm and expand upon these results, as well as to better evaluate potential differences between TEPNS and TDES. In addition, this study includes only adults (aged <60 years), which may limit the generalizability of the findings to older populations.

Furthermore, our study did not include a sham stimulation condition, as the primary objective was to compare the efficacy of two techniques already used in clinical practice for non-invasive diaphragmatic stimulation. Additionally, participant blinding was not feasible, since the stimulation methods (TEPNS and TDES) are applied to different anatomical locations, making it possible for participants to distinguish between the interventions.

Despite its limitations, this trial is expected to generate clinically relevant data, particularly regarding the safety of the interventions, which will be important to inform future studies in patient populations. The evidence generated by this trial will be especially important for advancing strategies aimed at mitigating respiratory muscle weakness.

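### The envelope is opened just before the baseline ultrasound, so the operator can know the first technique during the one outcome scan that could be acquired without that knowledge

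*Protocol article*

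**What the plan says.** All references are to the protocol article.

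- **Timing of disclosure** (Randomization and allocation): "Envelopes will be opened immediately prior to the baseline ultrasonography assessment". The envelopes are opaque and sequentially numbered, and they set the order of the two techniques 1:1.
- **Baseline as an outcome time point** (Diaphragmatic ultrasonography): the list of ultrasound time points begins "i) baseline (pre-intervention), (ii) 4–5 minutes into the intervention". It does not say whether baseline is repeated before the second technique.
- **Acquisition** (same section): "While blinding is not feasible during image acquisition". No exception is made for the baseline scan.
- **Reasons for not blinding participants**: under Blinding, "Blinding participants to the TEPNS or TDES intervention is not feasible, as most individuals can perceive the electrical stimulation", together with the need to see contractions to confirm placement; in the Discussion, "participant blinding was not feasible, since the stimulation methods (TEPNS and TDES) are applied to different anatomical locations".
- **Safeguards** (Blinding): "ultrasound images will be analyzed by a researcher who is blinded to the intervention procedure and image acquisition", and "all file names will be coded and will not indicate the group to which the participant was allocated". The Statistical analysis section adds a blinded statistician.
- **Analysis** (Statistical analysis): the primary analysis is a mixed model with fixed terms for treatment, period and sequence and a random participant effect. Percentage changes in thickness, thickening fraction and mobility are also planned, with no reference value named.

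**The concern.** In this trial, blinding protects the reading of images and the analysis but not their acquisition. During stimulation that is hard to avoid. Before the first stimulation it is not: no electrode is needed, no current flows, and the outcome views are the same right-sided ones whichever technique follows. Opening the envelope at that moment gives up, without a stated reason, the only scan in the session that could be acquired with the order unknown.

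At stake is the neutrality of the first baseline. If an operator who expects more from one technique handles the probe slightly differently before it, the baseline shifts in a way that depends on the technique. A blinded reader then measures the shifted image faithfully and cannot correct it. Any change calculated from that baseline carries the shift.

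**Working it through.** There is no planned figure to reproduce, since the article attaches no number to this point. The check sets the order of events against the blinding statements and then traces where a baseline error could go.

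**1. Is the operator exposed at the first baseline?** The envelope is opened before the scan, acquisition is described as unblinded, and no step assigns the scan to someone kept unaware of the order. So the operator can know.

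**2. Do the stated reasons cover this scan?** Perceived current and visible contractions arise with stimulation, and differing sites become apparent at set-up. None is present at a baseline taken before set-up.

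**3. Does the scan need the allocation?** The mobility and zone-of-apposition views are common to both techniques, and the Discussion says that one hemidiaphragm is assessed throughout. The technique-specific ultrasound, which locates the phrenic nerve for TEPNS or guides the electrodes for TDES, is set-up and can follow the opening.

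**4. What would a baseline error do to a percentage change?** Assume that the true change is nil and the acquired baseline is a fraction *e* too low. The apparent change is 1/(1 − *e*) − 1:

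| Assumed *e* | Calculation | Apparent change |
|---|---|---|
| 2% | 1/0.98 − 1 | +2.0% |
| 5% | 1/0.95 − 1 | +5.3% |
| 10% | 1/0.90 − 1 | +11.1% |

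The values of *e* are assumptions. Nothing in the article supports any particular size.

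**5. Does this reach the comparison of techniques?** Let X and Y be the values under TEPNS and TDES.

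- *One baseline B shared by both techniques.* The difference in absolute change is (X − B) − (Y − B) = X − Y, so the error cancels. The difference in percentage change is 100(X − Y)/B. The error rescales it by 1/(1 − *e*), but it cannot create a difference when X = Y.
- *A baseline in each period, with the same shift whichever technique comes first.* This acts as a period effect, and the balanced order and the period term deal with it.
- *A baseline in each period, with the first-period shift depending on the technique.* This does reach the contrast. The crossover estimate is half the sum of the two sequence-specific differences (TEPNS minus TDES). If only the sequence starting with TEPNS has a shifted first baseline, half of the apparent change enters. For *e* = 5%, that is (1/0.95 − 1)/2 = 0.0526/2, or about 2.6 percentage points. If the first baselines of the two sequences are shifted in opposite directions, the two halves add.

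**6. Does it reach the primary model?** That model names no baseline term or change score, so on the stated text no route is shown.

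**The case against.** The strongest reply is that the consequence is small and conditional. The primary model names no baseline, the sample size rests on the within-participant difference between conditions, and baseline as the reference for percentage change is a natural reading rather than a stated one. A single shared baseline would cancel from the difference in absolute change. If baselines are repeated, the second is acquired with the remaining technique known by elimination, so reordering protects only the first. All of this stands and limits the size of the point.

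A second reply is that the scan may come after set-up, in which case the allocation must already be known. The article does not give the sequence of set-up and baseline. This does not defeat the point, because set-up can be placed after the first baseline, but it does mean that the change is a reordering of the session and not only an edit.

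Three stronger readings are tempting and not supported:

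- *Allocation concealment fails.* It does not. The envelopes are opaque, numbered and opened after screening. The issue is possible bias in acquisition.
- *The participant also knows, and breathes differently.* The article does not say who opens the envelope or whether the participant is told. No step hides the order, but knowledge at that moment, and any effect on tidal breathing, are inferences.
- *The operator picks which images or cycles the reader sees.* The article says that all images are exported, that several cycles are averaged and that a blinded evaluator does the analysis. Operator selection is not described. What remains is probe handling, and there the article allows some latitude: a probe position roughly 0.5 to 2.0 cm below the costophrenic angle.

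**Conclusion.** The point holds as a minor one, with moderate confidence. The first baseline ultrasound can be acquired by an operator who knows the first technique, and the protocol's own reasons for not blinding do not cover that scan. The reading safeguards lower the risk but do not reach acquisition.

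The size of any bias is unknown. The percentages above show only what an assumed error would do. For the comparison of techniques to be affected, three conditions must hold together: percentage (or other) change is taken from baseline, a baseline is taken in each period, and the operator's handling differs by the technique to come. A reader might infer that the primary treatment estimate is biased. The stated model gives no ground for that.

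**What to change.** In Randomization and allocation, replace the sentence on timing with, for example: *The envelope is opened once the first baseline ultrasound is complete and its images are saved.* Add that technique-specific set-up (locating the phrenic nerve, or positioning the TDES electrodes) follows the opening. In Diaphragmatic ultrasonography, limit the statement that acquisition cannot be blinded to scans after that point.

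The cost is a small reordering of the session and a protocol amendment, which the section on modification of the protocol makes subject to formal approval. No visit, staff or procedure is added. Recruitment began in April 2024 and is expected to run to July 2027, so the change can protect only participants who enter after it. Any second-period baseline stays unprotected, as do the scans during stimulation.
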